### Statistical analysis

The data will be analyzed using SPSS version 20.0 software. Statistical significance is defined as *P* < 0.05. The methodology will be based on the Consolidated Standards of Reporting Trials Statement (CONSORT, http://www.consort-statement.org/consort-statement/) [26]. The full analysis population (including all subjects who will be randomized and will be at least evaluated at baseline) will be used in the primary analysis and the per protocol population (including all subjects who will be randomized and will not have major protocol deviations) will be used in the secondary analysis to assess the reliability of the results. Finally, missing data will be handled where possible using multiple imputations, and a sensitivity analysis will be performed. No interim analysis is planned.

The normality of the parameters will be estimated using frequency histograms and the Shapiro test. In case of nonparametric distribution, the data will be log transformed to obtain a normal distribution or nonparametric bootstrapping performed for cost data. In accordance with the distribution of the parameters, the baseline parameters will be presented separately for the control group and the experimental group: mean (standard deviation) or median (interquartile range) for continuous variables, proportions for categorical variables. Then, data will be compared between the two groups using Student’s t-test for continuous variables (durations), and chi-square or Fisher’s exact tests for categorical variables.

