### Interventions

#### Experimental group: screen-and-treat strategy

Pregnant women assigned to the intervention group are asked for a self-collected vaginal swab at randomization (Time 0). The self-collected vaginal swab has previously been demonstrated to have high validity and reliability compared to a practitioner-collected swab [17]. The swab will be immediately tested for *A. vaginae* and *G. vaginalis* using a systematic point-of-care screening test. Quantitative molecular analyses will be performed in laboratories that have experienced and national accreditation to realize point-of-care techniques. The quantitative real-time PCR (qPCR) method used to diagnose BV was previously described [11]. The result is reported as copies of microorganism DNA per 1 mL of vaginal suspension [9]. According to previous works [9, 11], BV will be defined by an *A. vaginae* load ≥ 10^8^ copies/mL and/or a *G. vaginalis* load ≥ 10^9^ copies/mL. The conclusion will be feedback of the positive or negative test result to the practitioner within less than 24 hours. In cases of positive diagnosis, the pregnant woman will be referred to an obstetrician, and an appropriate antibiotic treatment will be provided. The first intention for treatment of *A. vaginae* and *G. vaginalis* will be azithromycin (single dose, 1 g at day 1 and 1 g at day 3). The second choice for antibiotic treatment will be amoxicillin 2 g per day during 7 days in cases of known intolerance of azithromicin. The following procedure for women who are diagnosed positive is to perform a series of three successive screening controls until 28 weeks to detect either the failure of antibiotic treatment or a recurrence (that is, reappearance of bacteria from a control vaginal swab after therapy is stopped) (see Fig. 1). In cases of recurrence or treatment failure, a new antibiotic treatment will be provided, based on protocol guidelines (see Fig. 2). For women with a first negative diagnosis, the usual care management will be proposed.

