#### Control group: usual care management

No systematic vaginosis screening will be performed on the women assigned to the control group according to national and international guidelines [13, 19]. Usual pregnancy care includes 6 to 8 obstetrical consultations, no systematic vaginal swab, three ultrasound scans, 1st trimester Down syndrome screening and blood sampling for toxoplasmosis, syphilis, rubella, and complete blood group testing.

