### Data collection and follow-up

All data will be recorded from an electronic case report form (eCRF) specifically elaborated for the study (eCRF CleanWEB, Telemedicine Technologies S.A.S., www.tentelemed.com, 2015) and will be recorded at four specific study’s times as follows: randomization (T0), baseline assessment (T1), delivery (T2), and at 6 months after delivery (T3). All assessments are based either on medical files (pregnancy and delivery characteristics, obstetrical and neonatal outcomes), face-to-face questionnaires (smoking and alcohol habits, personal hygiene, pregnancies history or symptoms, and concomitant treatments such as treatment with pessary or progesterone), phone calls (to collect data on vaginal symptoms or potential side-effects of antibiotic) or self-report (health outcomes of their infant and health service use during the 6 months following the initial hospitalization). Details of the data recorded at the different times of the study are given in Table 3.

**Table 3 Tab3:** Data collection, instruments and assessment times

At randomization (T0)	Data on the health status of the participant and pregnancy characteristics will be collected from medical files of the practitioners. A face-to-face questionnaire will be also completed by all women and filled out by the midwife/obstetrician to collect specific data on demographics characteristics, smoking and alcohol habits, previous pregnancies and personal hygiene. The first vaginal swab will be collected by the practitioner and send to one of the two point-of-care laboratories associated to the study.
At baseline assessment – (during screening and treatment phases - T1)	Subsequent vaginal swabs will be realized during either routine pregnancy consultation or at the woman’s home depending on each participant schedule. In this later case, the sample will be sent by the women to the referent POC laboratory using a stamped, self-addressed envelope. Symptoms and potential side effects of antibiotics will be collected via a telephone interview. Participants will be informed via a phone call for subsequent vaginal swabs and treatment intake if needed.

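### Membership of the primary analysis set requires a baseline evaluation, but the only time point the protocol labels as baseline is T1, which follows randomisation and mainly concerns test-positive women in one arm

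*Protocol article*

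**What the plan says.** Under Statistical analysis, the protocol article uses the full analysis population for the primary analysis and defines it as "including all subjects who will be randomized and will be at least evaluated at baseline". The per-protocol population is secondary, and multiple imputation is planned for missing data where possible.

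Under Data collection and follow-up, the four recording times are "randomization (T0), baseline assessment (T1), delivery (T2), and at 6 months after delivery (T3". Randomisation and baseline are therefore two different times. Table 3 places the second of them "during screening and treatment phases - T1" and describes its content:

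- "Subsequent vaginal swabs will be realized during either routine pregnancy consultation or at the woman’s home depending on each participant schedule".
- "Symptoms and potential side effects of antibiotics will be collected via a telephone interview".
- Telephone calls to tell participants about further swabs and treatment intake.

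The Interventions section shows whom these procedures concern. In the experimental arm, "The following procedure for women who are diagnosed positive is to perform a series of three successive screening controls until 28 weeks"; but "For women with a first negative diagnosis, the usual care management will be proposed". In the control arm, "No systematic vaginosis screening will be performed on the women assigned to the control group".

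**The concern.** An analysis set that departs from all randomised women is safe only if the condition is settled before allocation, or cannot depend on allocation. Taken in the protocol's own vocabulary, the condition here refers to T1. That time comes after randomisation in an open-label trial, and its described procedures depend on the arm and on the test result. An analyst or database programmer who applied the label as written would filter on a post-randomisation event.

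The stakes are high because the planned difference is small: 4.3 % against 3.0 %, or 1.3 percentage points. The same difference is the denominator of the primary incremental cost-effectiveness ratio, so selection that shifted it would carry straight into the primary endpoint. Multiple imputation would not repair this, since it fills in outcomes for women in the set and cannot bring back women whom the set's definition has removed.

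**Working it through.** The plan gives no figure to reproduce on this point. The check sets the passages side by side and then works out what each reading implies.

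**Step 1. Which time carries the baseline label?** The schedule gives it to T1 only. T0 is called randomisation.

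**Step 2. Who has T1 content?** Subsequent swabs follow a positive test in the experimental arm. Side-effect calls and treatment-intake calls presuppose treatment. Test-negative experimental women return to usual care, and controls are not screened. The telephone collection of symptoms is not expressly limited to one arm, so some T1 contact with other women cannot be excluded.

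**Step 3. What does the T1 reading imply?** Inputs from the Sample size section are 3,400 women per group and an expected 10 % treated.

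- Experimental women with the described T1 procedures: 0.10 × 3,400 = 340.
- Controls with the described T1 procedures: none described.

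That cannot be squared with a two-arm comparison of 3,400 per group with 20 % loss to follow-up.

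**Step 4. What does the T0 reading imply?** Table 3 has a T0 questionnaire on demographics, smoking and alcohol, previous pregnancies and hygiene, completed by all women. The Statistical analysis section also plans to present baseline parameters for each group, which fits T0. On this reading the criterion is the same in both arms and is met around randomisation, so little selection is expected.

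Two small reservations remain. The order of the questionnaire and the allocation is not stated. The first swab also belongs to T0 and is asked of women assigned to the experimental arm, so a woman who declined it might be judged not evaluated, a hurdle that controls do not face.

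**Step 5. How sensitive is the planned effect to one-sided exclusion?** This is an illustration only. Assume no true effect, with 4.3 % preterm birth in both arms. Let a share f of the experimental arm alone be excluded, with preterm rate r among those excluded. The rate among those retained is (4.3 − f × r) / (1 − f). With r at twice the average, 8.6 %:

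| f | Retained rate | False reduction | Share of 1.3 points |
|---|---|---|---|
| 5 % | (4.3 − 0.43) / 0.95 = 4.07 % | 0.23 points | 17 % |
| 10 % | (4.3 − 0.86) / 0.90 = 3.82 % | 0.48 points | 37 % |

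A wider range of assumptions, f from 5 % to 20 % and r from 6 % to 10 %, gives false reductions from 0.09 to 1.43 points. The breadth of that range shows that the result is driven by the assumptions. Neither f nor r comes from the document, and the scenario matches neither the T1 nor the T0 reading.

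**The case against.** The strongest reply is that baseline plainly means T0. The same section speaks of baseline parameters for both groups, the usual baseline items sit in the T0 row of Table 3, and a reading that all but abolishes the control arm points to a mislabelled time rather than an intended analysis set. Table 3 does not separate the arms, the timing figure is not available here, and a fuller protocol or analysis plan may settle the boundary.

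Most of this stands. A reader might infer that the primary set *is* selected differently by arm, or that the primary comparison has lost the protection of randomisation. The document does not support that: it follows only if the criterion means T1, and the surrounding text favours T0. A reader might also take 0.23 to 0.48 points as the bias to expect. That is not supported either, since the exclusion share, its restriction to one arm and the doubled risk are all assumed. The Discussion's remark linking loss to follow-up with anxiety and low socioeconomic status does not fill the gap: it gives no preterm rate for lost women and no loss by arm.

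The stated rule itself survives the objection. It is written in this document, not left to another one. It never mentions T0, and it uses a label that the schedule attaches to a later visit. If every randomised woman has T0 data, the condition removes nobody and is not needed; if it does remove someone, it may do so after allocation is known.

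**Conclusion.** The point holds as a badly fixed definition of the primary analysis set. The criterion is not tied to T0, and the only time the protocol calls baseline is a post-randomisation one whose described content depends mainly on arm and test result.

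The consequence depends on the reading:

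- **If T1 is meant literally**, the set would be selected by arm and test result, leaving about 340 experimental women (assuming the planned 10 % treated) and few or no controls.
- **If T0 is meant**, as is more likely, little bias is expected and the fault is inconsistent labelling.

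No size of bias can be attributed to this plan. The calculation above shows only that selective exclusion in one arm could matter against a 1.3-point effect. Because the definition governs the primary comparison, it should be settled before analysis.

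**What to change.** Define the primary analysis set as all randomised women, analysed in the arm to which they were allocated, whatever their T1 status, at most excluding those who withdraw consent. Handle missing outcomes with the multiple imputation already planned. State that baseline data are those collected at T0, and rename T1, for example as the screening and treatment follow-up.

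The cost is a sentence in the Statistical analysis section and a changed label in the schedule and Table 3. No new data collection is needed for the effectiveness outcome, since delivery outcomes are taken from medical files with no restriction by arm.

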#### Secondary endpoints

The secondary endpoints are as follows:ICER per preterm birth avoided before 26, 28, 32 and 34 weeks.Obstetrical outcomes: rates of preterm birth before 26, 28, 32, 34, and 37 weeks of gestation, spontaneous abortion (between 14-22 weeks), late miscarriage (between 22-24 weeks), premature rupture of membranes, severe intrauterine growth restriction, preterm labor, duration of the woman’s hospitalization (that is hospitalization for delivery or preterm labor and potential previous hospitalizations due to gynecologic complications during pregnancy).Neonatal outcomes: neonatal mortality, neonatal morbidity (respiratory distress syndrome, bronchopulmonary dysplasia, necrotizing enterocolitis, periventricular leukomalacia), transfer to a neonatal intensive care unit (duration), mechanical ventilation (duration), congenital anomalies and duration of the newborn’s hospitalization.Treatment effectiveness: rate of recurrence (defined as a positive control vaginal swab using qPCR after the negativation of a precedent control vaginal swab), rate of treatment failure (defined as *A. vaginae* > 10^8^ copies/mL and/or a *G. vaginalis* load ≥ 10^9^ copies/mL from a control vaginal swab) and side effects associated with treatment.Other health care utilization: all the mother’s use of health care during the whole study period (for example, gynecologists and general practitioner consultations, hospital admission, clinical examinations and medications), as well as health care for the newborn (including neonatal care, re-hospitalization, medications, planned and non-planned consultations with pediatric practitioner or other specialists).

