### Sample size

The sample size was calculated from the expected differential ICER per preterm birth avoided between the two groups. In accordance with Briggs [22], the following hypothesis is stated: with an expected incremental rate of preterm birth of 1.3 % (4.3 % in the control group [23] and 3.0 % in the experimental group), an expected incremental cost of 230 euros (including cost of initial and following point-of-care tests and cost of treatments for 10 % of the women [24]), and an expected differential ICER at 22,500 euros corresponding to the avoided cost of a preterm birth before 37 weeks [25], with an 80 % statistical power and a threshold for statistical significance set at a *P* value of 0.05, and assuming that a potential 20 % of patients will be lost to follow-up, these calculations showed that 6,800 patients are needed (3,400 per group). Considering the potential of inclusion of each participating center, the inclusion duration will be planned over a 12-month period. The maximal period of participation for the included women is 12 months.

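### The log-transform rule cannot be applied to intensive-care and ventilation days, which will be zero for most newborns, and no handling of zeros is fixed

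*Protocol article*

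**What the plan says.** The Statistical analysis section of the protocol article sets out a sequence. First, "The normality of the parameters will be estimated using frequency histograms and the Shapiro test". Second, "In case of nonparametric distribution, the data will be log transformed to obtain a normal distribution or nonparametric bootstrapping performed for cost data". Third, "data will be compared between the two groups using Student’s t-test for continuous variables (durations"), with chi-square or Fisher's exact tests for categorical variables. It names no rank-based, two-part or raw-scale alternative for durations, and it does not say what happens to a value of zero.

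The Secondary endpoints section lists, among the neonatal outcomes, "transfer to a neonatal intensive care unit (duration), mechanical ventilation (duration"), and further on "congenital anomalies and duration of the newborn’s hospitalization". It does not say whether the first two durations are counted in every newborn or only in those transferred or ventilated.

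**The concern.** A log transformation followed by a t-test needs strictly positive values. Women enter this trial because their risk of preterm birth is low, so most of their newborns should never enter intensive care or need ventilation and will have zero days. The analyst then has to add a constant, drop the zeros or abandon the rule, and the article does not choose among these.

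The choices answer different questions. An added constant gives a result driven largely by how many newborns had any stay. Dropping zeros compares length of stay only among those admitted, a group formed after randomisation and possibly altered by the intervention. If screening prevented mainly milder cases, the infants still admitted would on average be sicker, and screening could look harmful while total days fell. The trial is open-label, so a choice left until the data are seen is a real weakness for outcomes meant to inform a screening recommendation.

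**Working it through.** The plan gives no figure for the share of zeros, so there is none to reproduce. All results below rest on stated assumptions plus the plan's own rates.

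**Inputs from the article (Sample size section).** Preterm birth "4.3 % in the control group [23] and 3.0 % in the experimental group"; 3,400 women per group; 20% loss to follow-up. Evaluable per arm: 3,400 × 0.80 = 2,720.

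**1. Share of newborns with zero days.** Let a be the proportion of preterm newborns with a stay, b the proportion of term newborns with a stay, and p the preterm rate. Share zero = 1 − [p·a + (1 − p)·b].

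| Assumed a, b | Control (p = 0.043) | Experimental (p = 0.030) |
|---|---|---|
| 0.30, 0.01 | 1 − (0.0129 + 0.0096) = 97.8% | 1 − (0.0090 + 0.0097) = 98.1% |
| 1.00, 0.10 | 1 − (0.0430 + 0.0957) = 86.1% | 1 − (0.0300 + 0.0970) = 87.3% |

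The range is therefore about 86% to 98%, and the log is undefined for all of these newborns.

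**2. Does an added constant restore normality?** With a stay in 4.3% of newborns (assumed lognormal, median 10 days, log-SD 1, rounded up to whole days), log(x + c) was tried for c from 0.001 to 1. Skewness was 4.6 to 5.2 and the Shapiro p-value was below 1e-74 throughout. The reason is simple. As c shrinks, log(x + c) behaves like a zero/non-zero indicator, whose skewness is (1 − 2p)/√[p(1 − p)] = 0.914/0.203 = 4.5 at p = 0.043. No constant in this range comes near the stated aim of a normal distribution.

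**3. Does the handling of zeros matter?** Simulation with 2,720 per arm and 1,000 trials per setting, a stay in 4.3% v 3.0% of newborns, the same assumed stay distribution, and two-sided p < 0.05:

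| Setting | Raw t-test | log(x + c), c = 1 to 0.01 | Log, zeros dropped |
|---|---|---|---|
| Stays equally long (median 10 days) | 37% | 67% to 73% | 5% |
| Longer experimental stays (median 16 v 10) | 6.5% | 28% to 53% | 90% |

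In the second setting the mean stay is the median × e^0.5, so mean days per newborn (before rounding up) are 0.043 × 10 × 1.649 = 0.71 in the control arm and 0.030 × 16 × 1.649 = 0.79 in the experimental arm. The raw mean is slightly higher under screening, while the log(x + 1) mean follows the lower share with a stay. The two differences had opposite signs in 57% of trials. For comparison, with no true difference (3.6% in both arms) they had opposite signs in 19%.

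**4. Direction of the selection when zeros are dropped.** Assume that screening cuts mild preterm births from 3.6% to 2.3% and leaves severe ones at 0.7%. The severe share among preterm infants rises from 0.7/4.3 = 16% to 0.7/3.0 = 23%, although no infant is harmed. In a simulation of this scenario (3,000 trials, 2,720 per arm), intensive-care days per 100 births fell from 51 to 44, yet the geometric mean stay among admitted infants rose from 5.8 to 6.8 days and was significantly longer under screening in 18% of trials. If all preterm and no term infants are admitted, those totals imply mean stays of about (51 − 44)/1.3 = 5.4 days for mild cases and (51 − 3.6 × 5.4)/0.7 = 45 days for severe ones.

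**5. Does the raw scale behave?** With no true difference, the raw-scale t-test rejected in 4.4% of 1,000 trials of zero-heavy durations, so its type I error holds at this sample size.

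**The case against.** Several stronger readings are tempting, and the article does not support them.

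- **Costs and the ICER.** A reader might infer that costs will be log transformed and that the sign of the cost difference could reverse. The sentence in the Statistical analysis section attaches bootstrapping to cost data, and the t-test is given for "t-test for continuous variables (durations"). The Cost-effectiveness analysis section builds the ICER on an untransformed difference in costs, with non-parametric bootstrapping for its uncertainty. What remains is a loosely worded 'or'.
- **Choice of test.** A reader might infer that Shapiro's test selects the test. It does not: Student's t-test is used for durations either way, and the check, which also uses histograms, decides only the scale. How readily Shapiro's test rejects for slight skewness is beside the point, because data this full of zeros fail any normality check.
- **All durations.** The woman's hospital stay is defined to include the delivery, and the newborn's stay is rarely zero. The problem fits two of the four listed durations.
- **Zeros silently dropped.** The article does not say so. Dropping them is one possible outcome of an unspecified step, and a separate analysis plan could fix it.

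It is also fair to say that the simulations use assumed distributions. With equal stay lengths, dropping zeros lost power and did not reverse anything; reversal needed further assumptions. Preferring raw means to a rank or two-part analysis is partly a matter of judgement.

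None of this rescues the rule for the two outcomes. A log-then-t instruction that cannot be carried out on most of the data is a stated rule that fails, and not merely a detail left to a later document.

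**Conclusion.** The point holds for two secondary outcomes, intensive-care duration and mechanical ventilation duration. As written, the rule cannot be applied to newborns with zero days, an added constant does not produce normality, and dropping zeros gives a comparison that randomisation no longer protects. The result then depends on an unstated choice: 5% to 73% of trials significant in one assumed setting, 6.5% to 90% in another, with conflicting signs in some scenarios.

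That zeros predominate is a sound inference from a low-risk population, but it is not a stated fact. The 86% to 98% range rests on assumed admission rates, and the rejection and sign figures rest on assumed stay distributions. That the log of zero is undefined rests on no assumption. The primary ICER, the sample size and the other two hospital-stay durations are not affected.

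**What to change.** In the Statistical analysis section, remove the normality-triggered log transformation for intensive-care and ventilation durations. State that mean days will be compared on the original scale over all newborns in the full analysis population, counting zero for those with no stay, with bootstrap (or Welch) confidence intervals. Report the proportion of newborns with any stay alongside. Length of stay among those admitted may be shown as description only.

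Add one sentence that costs are compared as arithmetic means with the bootstrap, as the Cost-effectiveness analysis section already implies.

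This costs only wording, since the bootstrap is already planned and no new data are needed. The price is some power when stays are highly skewed: in the equal-length setting the raw comparison reached 37% against 67% to 73% for the log with a constant. That extra power came from the difference in how many newborns had any stay, which the accompanying proportion reports directly.

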**Methods/Design:**

A multicenter, open-label randomized controlled trial (RCT) will be conducted in which 20 French obstetrics and gynecology centers will recruit eligible pregnant women at less than 20 weeks gestation with singleton pregnancy and with a low-risk factor for preterm birth. Interventions will include a) an experimental group that will receive a systematic rapid screen-and-treat program from a point-of-care analysis using a molecular quantification method and b) a control group that will receive usual care management. Randomization will be in a 1:1 allocation ratio. The primary endpoint that will be assessed over a period of 12 months will be the incremental cost-effectiveness ratio (ICER) expressed as cost per avoided preterm birth before 37 weeks. Secondary endpoints will include ICER per avoided preterm birth before 24, 28 and 32 weeks, obstetrical outcomes, neonatal outcomes, rates of treatment failure and recurrence episodes for positive women. Uncertainty surrounding these estimates will be addressed using nonparametric bootstrapping and represented using cost-effectiveness acceptability curves. A total of 6,800 pregnant women will be included.

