### Randomization

Computer-generated randomized lists were drawn up before the beginning of the study, using a permuted block design, under the responsibility of the clinical research unit (AP-HM). The randomization was stratified by center (1:1 allocation ratio).

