### Endpoints

#### Primary endpoint

The primary endpoint is the incremental cost-effectiveness ratio (ICER), expressed as the extra cost per additional preterm birth avoided before 37 weeks. The effectiveness criterion has been discussed and consensually approved by all the study’s main partners (gynecologist coordinator and co-coordinators, biologists, health economist and methodologist). We can assume that this intermediary criterion properly reflects short- and long-term prognosis of the children [20, 21].

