### Cost-effectiveness analysis

Incremental cost-effectiveness ratios (ICER) will be used to compare the cost and effectiveness of the experimental strategy with usual care. The ICER is the ratio of the difference between groups in costs to the difference in effectiveness. The difference in effectiveness equals the number of preterm births averted and is calculated as the number of preterm births in the screening group minus the number of preterm births in the control group. Thus, the ICER provides information on the potential acceptability of the intervention for decision makers. The costs perspective taken in our economic analysis is that of the healthcare payer. The time horizon started from the first prenatal consultation before the 20 weeks of gestation and ended at 6-months of age or death. The healthcare costs included are those that are likely to differ across the intervention and control groups. In our study, these costs are those associated with: screening using the point-of-care procedure (quantitative molecular analysis), control vaginal swabs for positive women, antibiotic treatments, antenatal hospital admissions, physicians’ consultations, management of complications, as well as neonatal costs for full term infants and preterm infants. Unit costs for health service use will be estimated using data from the French National Hospital Database (Programme de médicalisation des systèmes d’information, PMSI) and the National Tariff. Treatment costs were obtained from the French register of pharmaceutical specialties, an online database of information on healthcare products. The cost of the POC analysis using quantitative real-time PCR (qPCR) will be calculated using micro-costing technique, which is particularly well suited to evaluating the cost of an emerging technique [27]. The volume of resources used will be determined by direct observation of each stage of each testing procedure. Fixed and variable costs will be included. All resources will be valued in 2015/2016 euros, and the 12-month trial means there is no requirement to apply discounting. As the cost of preterm birth differs significantly according to the gestational age at birth [28–30], we will attempt to address this issue by calculating an ICER for specific birth gestational ages. Probabilistic sensitivity analyses, using the non-parametric bootstrap method, will be carried out to generate mean expected ICERs and to determine whether uncertainty or variation in the data used affect the ICERs [31]. In addition, cost-effectiveness acceptability curves were constructed to represent decision uncertainty surrounding cost-effectiveness estimates [32].

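### Randomisation is stratified by centre, but the named between-group tests ignore centre: a small, conservative loss of precision, mainly for durations

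*Protocol article*

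**What the plan says.** The Randomization section of the protocol article describes lists drawn up "using a permuted block design" and adds: "The randomization was stratified by center (1:1 allocation ratio". The abstract's Methods/Design paragraph gives the number of strata: "20 French obstetrics and gynecology centers will recruit eligible pregnant women".

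The Statistical analysis section first describes how baseline parameters will be presented. It then says that data will be compared between the two groups by "Student’s t-test for continuous variables (durations), and chi-square or Fisher’s exact tests for categorical variables". No stratified test and no model with a centre term is named anywhere in the article.

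The primary endpoint is handled separately: "The primary endpoint is the incremental cost-effectiveness ratio (ICER), expressed as the extra cost per additional preterm birth avoided before 37 weeks". Its uncertainty is addressed in the Cost-effectiveness analysis section: "Probabilistic sensitivity analyses, using the non-parametric bootstrap method, will be carried out to generate mean expected ICERs". Acceptability curves are also planned. That section does not mention centre.

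**The concern.** Stratified blocks make the arms nearly equal in size within each centre, so differences between centres largely cancel from the treatment comparison. An analysis that ignores centre does not know this. It counts the between-centre spread as noise and reports a standard error larger than the design delivers.

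The outcomes most exposed are those shaped by local practice. The Secondary endpoints section lists the mother's hospital stay, the newborn's hospital stay, and the durations of neonatal intensive care and mechanical ventilation. The volumes of hospital and neonatal care also feed the cost side of the ICER. What is at stake is wider confidence intervals than necessary for these outcomes. The validity of the comparisons is not in question.

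**Working it through.** **Inputs from the article.** 20 centres; permuted blocks, 1:1, stratified by centre; preterm birth rates of "4.3 % in the control group [23] and 3.0 % in the experimental group"; 6,800 women (3,400 per group) with 20% loss to follow-up; "Statistical significance is defined as *P* < 0.05", with sidedness not stated (two-sided is used below).

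Evaluable women: 3,400 × 0.80 = 2,720 per arm, 5,440 in total.

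**Inputs assumed.** The article gives no between-centre variance and no ICC, so ranges are shown.

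**The plan's own figure.** The sample size of 6,800 is described as ICER-based. It cannot be reproduced on that basis, because no cost standard deviation and no cost-effect correlation are given. A comparison of the rates alone at 80% power, one-sided 5% and with continuity correction comes close: 2,724 per arm, 2,724 / 0.80 = 3,405, total 6,810. The figure matters here only because it fixes the number of evaluable women.

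**Durations.** Let the total variance be σ² and the share due to centre be ICC. With arms balanced within centres:

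- true variance of the difference in means: 2σ²(1 − ICC)/n
- variance assumed by the unstratified t-test: 2σ²/n
- ratio of standard errors: 1/√(1 − ICC)
- true type I error: 2[1 − Φ(1.96 × ratio)]
- power where a centre-adjusted analysis has 80%: 1 − Φ(1.96 × ratio − 2.80), with 2.80 = 1.96 + 0.84

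| Assumed ICC | SE overstated by | True type I error | Power (adjusted analysis: 80%) |
|---|---|---|---|
| 0.01 | 0.5% | 4.9% | 79.7% |
| 0.02 | 1.0% | 4.8% | 79.4% |
| 0.05 | 2.6% | 4.4% | 78.5% |
| 0.10 | 5.4% | 3.9% | 76.9% |
| 0.20 | 11.8% | 2.8% | 72.9% |

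For example, at ICC 0.10 the ratio is 1/√0.90 = 1.054.

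**The same effect in women.** Ignoring a centre share s of the variance is equivalent to discarding s × 5,440 women: 0.02 × 5,440 = 109 and 0.10 × 5,440 = 544. This differs from the number of extra women needed to compensate, 5,440 × [1/(1 − s) − 1], which is 111 to 604.

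**Preterm birth.** A simulation used 20 equal centres, 2,720 women per arm, rates of 4.3% and 3.0%, and 20,000 replicates per scenario. It compared the unstratified chi-square test with the Cochran-Mantel-Haenszel (CMH) test by centre, both two-sided.

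| Assumed between-centre SD (logit scale) | Unstratified SE / stratified SE | Power, unstratified | Power, CMH |
|---|---|---|---|
| 0 | 1.000 | 72.7% | 72.7% |
| 0.25 | 1.001 | 72.4% | 72.4% |
| 0.50 | 1.004 | 72.5% | 72.7% |
| 0.75 | 1.011 | 72.8% | 73.3% |
| 1.00 | 1.020 | 72.0% | 73.1% |

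Unequal centre sizes give the same picture. The simulated type I error of the unstratified test lay between 4.4% and 5.1%. Monte Carlo error is about 0.15 points for type I error and 0.3 points for power.

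**The case against.** The strongest reply is that an article condenses a fuller protocol, that a statistical analysis plan may add centre adjustment, and that the effect is too small to matter. On the first two points, the article is not silent: it names three specific tests, and none uses the strata. A later plan that adjusts for centre would be changing a published method. On size, the reply is largely right for preterm birth. For durations it depends on a variance that nobody has stated.

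A reader might also infer more than the article supports:

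- **That the inference is invalid.** It is not. The standard errors err on the large side, so false positives are not inflated. Loss of precision and misstated standard errors are one effect here, not two.
- **That the primary analysis is wrong.** The named tests serve baseline and secondary comparisons. The ICER rests on the bootstrap, and the article says nothing for or against resampling within centre. That is silence, not a stated error.
- **That unit costs differ between centres.** The Cost-effectiveness analysis section values health-service use from a national hospital database and the National Tariff. Between-centre cost variance would have to come from resource volumes and case mix.
- **That stratifying would repair a power shortfall.** With 2,720 per arm, a test of the rates alone has 72.5% power two-sided and 81.9% one-sided. The article's 80% refers to an ICER-based calculation with no stated sidedness. That is a separate question, and stratification moves power by about one point at most. Nor can the net benefit be judged against its standard error, because no cost standard deviation is given.

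**Conclusion.** The mismatch between design and named analysis is real, but minor. For preterm birth, even strong assumed heterogeneity between centres changes little. For durations, and for costs driven by resource use, the gain could be worth having if the centre share of variance approaches 10%. It is trivial if that share is about 1%.

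The conclusion rests on near-equal arms within each centre, which permuted blocks should give, and on assumed ranges for the ICC and the between-centre logit SD. The direction does not depend on those ranges; the magnitude does. The case for acting is that the correction is almost free, not that the current plan would mislead.

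**What to change.** Replace the unstratified comparisons in the Statistical analysis section with centre-stratified ones:

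- **Binary outcomes, including preterm birth:** Mantel-Haenszel risk difference across centres, or the CMH test.
- **Durations and costs:** linear models with centre as a factor.
- **Bootstrap for the ICER and acceptability curves:** resample women within centre and arm, so that the economic analysis follows the same structure. This is for consistency and does not correct a stated error.
- **Very small centres:** pool them by a rule fixed before outcome data are analysed by arm. In an open-label trial, that is the meaningful time point.

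The cost is a few sentences of text. No extra data or participants are needed, since centre defines the randomisation lists. The pooling rule is the only downside.
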